**Discussion:**

With no standardized treatment for IVH and a poor prognosis, new treatments are needed. IVH patients often need CSF drainage to treat hydrocephalus and to decrease ICP. Standard treatment with passive external ventricular drainage is related to an increased risk of infections which is found in up to 22% of treated cases. The passive VC is known to have a risk of occlusion and is seen in 19–47% of the cases.

We hypothesize that the use of active fluid change using the IRRAflow system will be safe and feasible and will reduce the occlusion and infection rates in patients with IVH.

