## Methods and study design

This current phase 2 and feasibility study evaluates the IRRAflow system. A closed system VC with active irrigation and aspiration in comparison to standard passive external ventricular drainage (Fig. 1). We hypothesize that closed system active irrigation will be safe to use and will reduce the occlusion and infections rates and increase clearance rate and clot removal. The framework of the trial is to test the superiority of IRRAflow compared to EVD treatment. This manuscript is based on protocol version 4.0 dated 16th of January 2022. Important amendments to the protocol will be added and shown in clinicaltrials.gov.

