#### Sample size and statistical considerations

The sample size of the study was determined based on the primary outcome. We considered a two-sided log-rank test for comparison of the time-to-catheter occlusion between the two treatment groups. Furthermore, we assumed an equal length of follow-up together with an occlusion risk of 10% and 35% in the intervention and control groups. Patient mortality was assumed to be independent of the considered time to catheter occlusion and to correspond to a 30% dropout. We used a significance level of 20% due to the exploratory nature of the study. Then, for a power of 80%, Schoenfeld’s approach resulted in a required sample size of 58 (i.e., 29 subjects with drain per treatment group).

Data will be analyzed according to the intention-to-treat principle. For the primary outcome (time to catheter occlusion), time-to-event analysis will be used, in which drains are considered the basic experimental units. Times corresponding to drains without occlusion during follow-up will be considered censored. Especially, since catheter occlusion is independent of patient mortality, patient death is treated as a censoring event. Time to occlusion will be described by Kaplan-Meier plots and investigated by Cox regression. Estimated beneficial treatment effects with a two-sided *p*-value ≤ 20% will be considered an interesting finding worth further investigation.

Further outcome measures (secondary/exploratory) will be used for descriptive and exploratory purposes only; no formal statistical hypotheses will be tested.

Secondary endpoints (subject-based unless otherwise specified) will be handled as follows:

Kaplan-Meier estimates and Cox regression will be used to describe the time to recurrence of hemorrhage and time to death (with a follow-up time of 3 months).

Occurrence of catheter-related infections and shunt dependency will be reported as proportions, and length of stay in ICU will be reported as means. Clearance of ventricular blood will be described with the help of linear mixed effect models. Measures of functional status will be dichotomized and analyzed by baseline-adjusted logistic regression. All estimates will be reported together with corresponding confidence intervals (CIs).

Exploratory endpoints (mainly drain-based) will be handled as follows:

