Proportions and CIs will be reported for technical success, procedure success, and necessity of revision procedures. Procedure time, duration of VC in place, and number of required flushes will be described by means and CIs.

Reported CIs will include a Bonferroni adjustment to maintain the family-wise coverage probability at 95%.

We expect based on our prior experiences that the proportion of missing values in this study will be very low and that missing values occur completely random. All statistical analyses will be run as complete case analyses.

For early safety monitoring, an interim analysis is done when 20 subjects have been enrolled in the study (10 subjects per arm). The analyses will be performed in an intent-to-treat fashion.

Monitored safety outcomes are mortality as well as the total number of adverse and serious adverse events related to catheter treatment (infections, bleedings in relation to intervention, displacements of catheters, catheter misplacement). For *p*-values below 20%, an early stop of the study will be considered (non-binding); otherwise, the study continues until the study end.

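### Infection reduction is a stated hypothesis, but infection is planned only as proportions with confidence intervals, and no between-arm effect measure is named

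*Protocol article*

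**What the plan says.** The hypothesis appears twice in the protocol article. The abstract's Discussion says that active fluid exchange "will reduce the occlusion and infection rates in patients with IVH". Methods and study design says that it "will reduce the occlusion and infections rates and increase clearance rate and clot removal", and adds: "The framework of the trial is to test the superiority of IRRAflow compared to EVD treatment". Catheter-related infection is listed under Secondary endpoints.

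The section Sample size and statistical considerations sets out the analysis:

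- **Infection, shunt dependency, ICU stay:** "Occurrence of catheter-related infections and shunt dependency will be reported as proportions, and length of stay in ICU will be reported as means".
- **Recurrent haemorrhage and death:** Kaplan-Meier estimates and Cox regression.
- **Clearance of blood:** linear mixed models.
- **Functional status:** baseline-adjusted logistic regression after dichotomising.
- **Intervals:** every estimate carries one, with a Bonferroni adjustment to a family-wise 95%. The number of intervals in the family is not given.
- **Status of outcomes other than the primary:** they "will be used for descriptive and exploratory purposes only; no formal statistical hypotheses will be tested".

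**The concern.** Infection is the only outcome named in the hypothesis, other than the primary one, for which the plan names no method that yields a treatment effect. Clearance, which the hypothesis also names, has a mixed model. Infection has a proportion.

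A hypothesis that one arm has a lower rate than the other concerns a contrast. The quantity that answers it is a difference or ratio with its own interval. Two separate intervals for two proportions do not supply that interval.

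The direction of the effect is also open. The Discussion notes that IRRAflow is tunnelled and sutured, while the standard EVD is fixed by a bolt, and that earlier studies found bolt fixation to reduce infection. A reader therefore needs to see both how much benefit and how much excess infection the data leave open. The planned output does not show this directly.

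**Working it through.** **1. The plan's own figure.** The only stated figure is the sample size for occlusion. The inputs, all from Sample size and statistical considerations, are risks of 10% and 35%, two-sided alpha 0.20, power 80%, 1:1 allocation and 30% dropout.

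- Hazard ratio = ln(0.90)/ln(0.65) = 0.2446.
- Events (Schoenfeld) = 4 × (1.2816 + 0.8416)² / ln(0.2446)² = 9.09.
- Patients = 9.09 / 0.225 = 40.4, where 0.225 is the mean of 10% and 35%.
- After dropout = 40.4 / 0.70 = 57.7, so 58.

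The figure reproduces. Infection plays no part in it, so this point does not touch it.

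**2. The interval the plan does not name.** The counts are assumed for illustration: 3 infections among 29 in each arm (10.3%, close to the 10% ventriculitis rate in the Background).

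- Wilson limits for 3/29, with p = 0.10345 and z = 1.96. Centre = (0.10345 + 3.841/58)/(1 + 3.841/29) = 0.1498. Half-width = 1.96 × √(0.10345 × 0.89655/29 + 3.841/(4 × 841))/(1 + 3.841/29) = 0.1140. Limits: 3.58% to 26.39%.
- Newcombe interval for a difference of 0: ± √[(0.10345 - 0.03581)² + (0.26385 - 0.10345)²] = ± √(0.00457 + 0.02573) = ± 0.174.

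The difference is 0, with an unadjusted 95% interval of -17.4 to +17.4 points. Equal observed proportions would still be compatible with an excess or a reduction of about 17 points.

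**3. With the plan's Bonferroni adjustment.** The family size is not stated, so a range of 3 to 12 intervals is assumed. Repeating step 2:

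| Assumed family | z | 3/29 v 3/29 |
|---|---|---|
| 1 (unadjusted) | 1.960 | -17.4 to +17.4 |
| 3 | 2.394 | -21.8 to +21.8 |
| 12 | 2.865 | -26.7 to +26.7 |

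**4. What a contrast could achieve with 29 per arm.** The control rates are the article's own (10% in the Background, up to 22% in the main Discussion). A halving under IRRAflow is assumed. Unadjusted Wald half-width = 1.96 × √[p0(1 - p0)/29 + p1(1 - p1)/29].

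| EVD v IRRAflow | Difference | 95% half-width | Power, alpha 0.20 | Power, alpha 0.05 |
|---|---|---|---|---|
| 10% v 5% | 5 points | 13.5 points | 29% | 11% |
| 22% v 11% | 11 points | 18.9 points | 44% | 20% |

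The contrast can be estimated, but only imprecisely. The power figures describe what a test would do; the plan intends no test.

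**The case against.** The strongest defence is that the article condenses a fuller protocol, that a separate analysis plan may exist, and that the choice of effect measure and interval method is often left to it. The article also states openly that secondary outcomes are descriptive. Proportions from two randomised arms give the point difference by subtraction, and a reader with the counts can compute an interval.

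Much of this stands, and it limits the point. Three stronger readings might be inferred, and the documents do not support them.

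- **That no between-arm infection effect will be estimated, so the hypothesis goes unanswered.** The article names no contrast; it does not rule one out. Per-arm proportions with intervals are informative in a descriptive way.
- **That the mismatch covers all three endpoints in the sentence.** The hypothesis names occlusion, infection, clearance and clot removal. Shunt dependency and ICU stay are not in it.
- **That the plan will judge infection by whether the intervals overlap, and so miss real differences.** Nothing in the article proposes this. A tempting example, 4/29 under EVD v 0/29 under IRRAflow, does not show it either. The exact single-arm intervals (3.9-31.7% and 0-11.9%) overlap, but the unadjusted Newcombe interval for the difference, -30.6 to +0.5 points, also includes zero. The rule that just-touching 95% intervals correspond to p of about 0.006 needs equal widths, which these are not.

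Two parts of the defence do not hold. First, the article does go to method level for the neighbouring outcomes, so a summary by proportions is a stated choice and not just silence. Secondly, having no formal tests does not exclude an estimated difference: the Cox and logistic models stand under that same declaration. The interim look does not fill the gap, because it counts infections only within a pooled total of catheter-related events, for safety, at 20 patients.

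**Conclusion.** The point holds in a limited form. Infection reduction is hypothesised under a superiority framework, yet the planned output names no between-arm measure for it, while other outcomes in the same section get models that can supply one. What is lost is a planned interval for the difference. In the illustration that interval is about ±17 points unadjusted, and ±22 to ±27 points for an assumed family of 3 to 12 intervals. These widths rest on assumed counts and on all 29 patients per arm being evaluable for infection.

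This is a minor reporting matter. A contrast will not settle the infection question at this sample size, but its interval would show plainly how little is settled. The primary analysis and the sample size stand.

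**What to change.** In Sample size and statistical considerations, or in the analysis plan:

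1. Beside the per-arm proportions, report the infection risk difference (IRRAflow minus EVD) with an interval suited to small counts, such as Newcombe's, at the plan's Bonferroni-adjusted level.
2. State that the infection hypothesis is exploratory and is read from that interval.
3. Optionally, for consistency, add the risk difference for shunt dependency and the mean difference for ICU stay, each with its interval.

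The cost is a few lines of text. No further data, patients or change to the primary analysis are needed.

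### The number of flushes is summarised as a raw mean with no allowance for time in place, so the arm means mix flush need with exposure and could mislead in either direction (minor)

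*Protocol article*

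**What the plan says.** The protocol article lists the number of flushes among its exploratory endpoints, without a time unit. Duration of drainage, in days, is a separate endpoint in the same list. The statistical section introduces the exploratory block with "Exploratory endpoints (mainly drain-based) will be handled as follows" and then fixes the summary: "Procedure time, duration of VC in place, and number of required flushes will be described by means and CIs". No rate, offset or drain-time denominator is mentioned.

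The same section limits what these results are for. Secondary and exploratory outcomes "will be used for descriptive and exploratory purposes only; no formal statistical hypotheses will be tested".

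For the primary endpoint, the section assumes "an occlusion risk of 10% and 35% in the intervention and control groups" and treats drains that do not occlude, and deaths, as censored.

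**The concern.** The expected flush count for a drain is its flush rate multiplied by its time in place. A mean count answers a question about need only if time in place is similar in the two arms, and nothing in the plan ensures that. Occlusion, the event the device is meant to prevent, can end a drain early. A replaced drain may enter as two short drains with two low counts. Death shortens exposure, and so would earlier removal after faster clearance. The primary endpoint handles unequal observation time by censoring, but the flush count has no counterpart to this.

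Readers will set the two arm means side by side whether or not a test is planned. They could then take a difference in drain survival for a difference in flush need, or overlook a real difference in need because exposure offsets it.

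**Working it through.** **Inputs from the protocol article.** Occlusion risks 10% (IRRAflow) and 35% (EVD); two-sided significance level 20%; power 80%; dropout 30%; 1:1 allocation; N = 58. No flush rate and no expected drain duration is given.

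**Assumptions made here.** Constant hazards, a common planned removal time T in both arms, and the same true daily flush rate in both arms. T = 8 days is used only to show days; the ratios do not depend on T.

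**Step 1: the plan's own figure.** There is no stated flush figure to reproduce, so the sample size serves as a check that the risks are read as intended.
- Cumulative hazards: −ln(0.90) = 0.1054 and −ln(0.65) = 0.4308. Hazard ratio = 0.1054/0.4308 = 0.2446.
- Schoenfeld events: 4 × (1.2816 + 0.8416)² / (ln 0.2446)² = 9.09.
- Divided by the mean risk 0.225: 40.4. Divided by 0.70: 57.7, which rounds up to 58. The stated figure reproduces.

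**Step 2: occlusion ends the drain, no replacement counted.** Mean drain time = T × risk / cumulative hazard.
- IRRAflow: 0.10/0.1054 = 0.949 T (7.59 days at T = 8).
- EVD: 0.35/0.4308 = 0.812 T (6.50 days).
- Ratio: 0.949/0.812 = 1.17.

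At an assumed one flush per day in both arms, the raw means are 7.6 and 6.5 flushes. IRRAflow shows the higher raw mean whenever its true rate ratio lies between 1/1.168 = 0.856 and 1. Below 0.856 the raw means rank the arms correctly.

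**Step 3: every occluded drain is replaced at once and each drain is a unit.** Expected drains per patient over T = 1 + cumulative hazard.
- EVD 1.431, IRRAflow 1.105.
- Ratio of mean days per drain: 1.431/1.105 = 1.29.
- Break-even rate ratio: 1.105/1.431 = 0.77.

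**Step 4: sensitivity.**
- *Death.* If the 30% dropout is read as equal mortality over T, the chances of reaching T with the drain open are 0.90 × 0.70 = 0.63 and 0.65 × 0.70 = 0.455. The Step 2 ratio becomes (0.37/0.4620)/(0.545/0.7875) = 0.801/0.692 = 1.16, almost unchanged. Unequal mortality would shift it either way.
- *Few replacements.* The Background section can be read as saying that 19% of occlusions lead to replacement. If only those end the drain and the rest stay in, the ratio is (1 + 0.19 × 0.35)/(1 + 0.19 × 0.10) = 1.0665/1.019 = 1.05.
- *Earlier removal on IRRAflow.* With the Step 2 hazards, mean drain time is equal when 1 − exp(−0.1054 f) = 0.1054 × 0.812, that is f = 0.85, where f is IRRAflow's planned removal time as a fraction of EVD's (about 6.8 against 8 days). Removal earlier than that reverses the distortion in favour of IRRAflow.

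**The case against.** Five objections have force.

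1. **Nothing is tested.** The plan describes the flush count and attaches no hypothesis or decision to it. Total flushes is also a legitimate quantity in its own right, as workload or number of manipulations. This stands, and it limits the severity.

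2. **Duration is reported in the same sentence.** A reader can divide mean flushes by mean duration and obtain a crude daily rate, provided both are summarised on the same drains. This stands in part: the quotient has no valid confidence interval and makes no allowance for several drains per patient.

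3. **Per-drain counting is inferred.** The block is only mainly drain-based and does not assign a unit to flushes. If counts were totalled per patient, the replacement mechanism would drop out, but length of drainage and death would still alter exposure.

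4. **A constant flush rate is assumed.** If flushes cluster around impending blockage, the count need not grow in proportion to days. This stands as a limit on the illustration.

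5. **It could be left to the analysis plan.** A condensed article need not give offsets or variance estimators. But the article does state a summary, a mean, and that summary is the one at issue.

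A reader might go further and infer that the raw mean is bound to make the better device look worse, perhaps by as much as 50%. The documents do not support this. They give no expected drain duration for either arm, and the sample-size text says "we assumed an equal length of follow-up". The device description rests on faster washout, which could end drainage sooner on IRRAflow. A 50% excess needs drain lives in a ratio of 1.5, such as 9 against 6 days, which appears nowhere in the article and exceeds what its occlusion risks give under the assumptions above. Nor does the article suggest that the device's automatic irrigation cycles would be counted as flushes.

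**Conclusion.** The point holds as a minor one. The stated summary mixes flush need with time in place, and the distortion can run either way. With the plan's 10% and 35% risks, constant hazards, a common planned removal time and equal daily need, IRRAflow would show a spurious excess of about 17%, rising to about 29% if every occluded drain is replaced and each is counted. The excess would be smaller if most occluded drains stay in place, and it would reverse if drainage on IRRAflow ends sufficiently earlier. The primary analysis, the sample size of 58 and the safety monitoring are not affected.

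**What to change.** Keep the raw mean and add one line to the analysis text: report flushes per drain-day in each arm (total flushes divided by total drain-days), with a rate ratio and a confidence interval that allows for several drains per patient. A Poisson model with log drain-time as offset and errors clustered by patient would do. State at the same time whether the raw mean is per drain or per patient.

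Both the count and the duration are already planned endpoints, so no new data are needed. The cost is slightly more analysis. With 29 patients per arm the variance estimates will be imprecise, so the interval should be read as descriptive, like the other exploratory results.

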## Abstract

**Background:**

Primary intraventricular hemorrhage (IVH) or IVH secondary to intracerebral (ICH) and subarachnoid hemorrhage (SAH) are known to have a very poor prognosis, with an expected mortality between 50 and 80% (Hinson et al. Current Neurology and Neuroscience Reports 10:73–82, 2010). Clearance of IVH might improve patient outcome.

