## Background

Primary intraventricular hemorrhage (IVH) or IVH secondary to intracerebral hemorrhage (ICH) and subarachnoid hemorrhage (SAH) with extension to the ventricles are known to have a very poor prognosis, with expected mortality between 50 and 80% [1]. Yet, therapy directed at ameliorating intraventricular clot has been limited. IVH often results in increased intracranial pressure (ICP) by direct mass effect, by obstruction, and further by creating edema around the hematoma. These conditions can be complicated by hydrocephalus caused by CSF malabsorption [2] or obstruction of CSF pathways. Further secondary brain injury is related to the clotting cascade after endothelial damage and hemoglobin breakdown [3]*.* Thrombin causes inflammatory cells to infiltrate the brain, proliferation of mesenchymal cells, formation of brain edema, and scar tissue [3]*.* Thrombin binds to protease-activated receptors *(1)* and activates the central nervous system microglia and complement cascade. As a result, multiple immune pathways are activated, which contributes to apoptosis and necrosis. Heme influx in neurons after endothelial damage leads to iron release and neuronal insult [3].

CSF drainage is a key factor in maintaining acceptable ICP levels to prevent secondary brain damage. There are multiple approaches to facilitating CSF drainage and monitoring ICP. A ventricular catheter (VC) inserted into the lateral ventricle allows for drainage of CSF, but complication rates are high. VC occlusions in patients with IVH have been reported in 41% [4], of these 19% are having at least one VC replacement [4]. VC-related infection rates are found to be 10% for bacterial ventriculitis [5, 6].

The aim of this study is to evaluate the safety and feasibility in the use of active fluid exchange in the treatment of intraventricular hemorrhage.

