#### Follow-up assessments

After placement of the VC, the patients in the two arms will receive the same treatment and monitoring. They will be admitted to the intensive care unit and later transfer to the stationary neurosurgical department before discharge to a rehabilitation facility. Patients will be followed closely regarding the primary, secondary, and exploratory endpoints. During the admission period, the patients will be followed with a CT scan at day 0, day 2, day 4, day 6, and day 8 to evaluate the size of the hematoma using CT volumetrics.

A scheduled follow-up will be applied for all included patients including a clinical status at the time of inclusion, discharge, and 3 months post-procedure. The follow-up will include GCS and mRS at inclusion, discharge, and 3 months. Furthermore, eGOS will be evaluated at discharge and 3 months. The rate of shunt dependency, adverse events, and serious adverse events will be evaluated continuously during the inclusion period. Mortality rates will be evaluated at 30 days and 3 months.

All patients will receive best practice care following trial exclusion or termination. Post-trial care will be independent of trial participation and similar to the care offered to patients who were not enrolled or withdrew consent. Patients who are harmed during the trial will not be offered compensation, which is specific for the trial. However, patients might be eligible for compensation under similar rules and conditions as patients who are not enrolled in the trial as defined by Danish law (Patienterstatningen).

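### The plan assumes few, completely random missing values and complete-case analysis throughout, although it is sized for 30% loss to death and death or withdrawal cuts short the CT series for blood clearance

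*Protocol article*

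**What the plan says.** All references are to the protocol article.

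- **Missing data** (Sample size and statistical considerations). From earlier experience, the authors anticipate hardly any gaps in the data. The mechanism and the handling rule are stated as follows: "missing values occur completely random. All statistical analyses will be run as complete case analyses". No analysis is exempted.
- **Mortality in the sample size** (same section). "Patient mortality was assumed to be independent of the considered time to catheter occlusion and to correspond to a 30% dropout". The Background describes the disease as having a "very poor prognosis, with expected mortality between 50 and 80" percent; neither figure has a time horizon.
- **The endpoint.** Clearance is listed among the secondary endpoints as the absolute blood volume in ml on head CT. Under Follow-up assessments, during admission "the patients will be followed with a CT scan at day 0, day 2, day 4, day 6, and day 8".
- **The model.** "Clearance of ventricular blood will be described with the help of linear mixed effect models".
- **Other relevant rules.** Data are to be analysed by intention to treat. Death is a censoring event for time to occlusion, and time to death has its own analysis. Neither rule covers CT volumes. The section on withdrawal says that no data are collected after consent is withdrawn, and consent is sought only after the catheter has been placed.

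**The concern.** A trial enlarged to absorb 30% loss to death cannot comfortably assume that measurements which stop at death will be nearly complete. Nor is the loss likely to be unrelated to the measurement. The abstract's rationale is that "Clearance of IVH might improve patient outcome", and the Discussion cites an earlier trial in which greater clot removal went with better functional outcome. If blood burden is related to prognosis, patients whose scan series ends early probably differ in volume from those scanned through day 8.

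The handling rule rests on that premise. A linear mixed model fitted by likelihood uses whatever scans a patient has, and it is valid under missing at random, a weaker assumption. A patient-level complete-case rule removes this advantage: a patient who dies on day 7 with scans at days 0, 2, 4 and 6 would contribute nothing. At stake is whether the clearance estimates and their confidence intervals describe all randomised patients or a selected subset.

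**Working it through.** **1. Is the 30% really part of the design?** Inputs from the sample-size paragraph: occlusion risks 10% and 35%, two-sided alpha 20%, power 80%, 1:1 allocation, 30% dropout from death.

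- Hazard ratio = ln(0.90)/ln(0.65) = 0.2446.
- Schoenfeld events = (z0.90 + z0.80)² / (0.25 × ln(HR)²) = 9.09.
- Mean event probability = (0.10 + 0.35)/2 = 0.225, so patients = 9.09/0.225 = 40.4.
- Allowing for dropout: 40.4/(1 − 0.30) = 57.7, rounded up to 58.

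The stated 58 is reproduced with the 30% loss included; without it, the same calculation gives 40.4. Substantial loss to death is therefore built into the plan's own number.

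**2. The statements side by side.** One paragraph plans for 30% loss through death. A later one expects very few missing values, arising completely at random. Both can hold for an outcome recorded before deaths occur, or for time to event with censoring. They do not sit together for a volume measured repeatedly up to day 8, unless almost no one dies or withdraws by then. The document does not say that.

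**3. Patients left under patient-level deletion.** Remaining = 58 × (1 − m), where m is the proportion dead by day 8. The document does not give m, so the values below are assumptions. Withdrawal and other missed scans are ignored.

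| Assumed m | Remaining of 58 | Per arm (of 29) |
|---|---|---|
| 10% | 52.2 | 26.1 |
| 20% | 46.4 | 23.2 |
| 30% | 40.6 | 20.3 |

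The last row puts the whole planning figure before day 8 and is a worst case for it.

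**4. Does the rule matter for the estimate?** An illustrative simulation was run, with assumptions that are not from the document: one data set of 3,000 patients, five scans each, mean day-0 volume about 30 ml, true slopes −1.5 (control) and −2.5 (intervention) ml/day, and a death hazard rising with the last observed volume, giving 31% dead by day 8.

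| Data used | Control slope | Intervention slope | Difference |
|---|---|---|---|
| All scans, as if no one died | −1.50 | −2.49 | −0.99 |
| Mixed model, available scans | −1.50 | −2.51 | −1.01 |
| Mixed model, complete cases | −1.62 | −2.58 | −0.97 |

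Mean day-0 volume was 29.7 ml in all patients and 26.8 ml in complete cases. Complete cases thus started with less blood and overstated clearance in both arms, while the arm difference hardly moved. When death was unrelated to volume (24% dead by day 8), the complete-case slopes were −1.52 and −2.48, nearly unbiased. This shows a mechanism only; it does not estimate the bias in this trial.

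**The case against.** **The rule may not mean patient-level deletion.** A reader might infer that the clearance model will keep only survivors. The text does not establish this. It does not say whether a case is a patient or a scan, and a mixed model works on scan-level rows. If the sentence only means no imputation, patients who die contribute scans until death and the main fix is already in effect. This objection stands against any flat statement that only survivors are analysed. It does not rescue the completely-at-random claim, which is unsupported under either reading, and the ambiguity itself needs resolving.

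**The mortality figures do not give day-8 losses.** One might apply the Background's 50–80% and conclude that 29 (58 × 0.5) or 12 (58 × 0.2) patients would remain. The document does not support that. The range is a general prognosis without a time horizon, whereas the trial requires an indication for active treatment and excludes patients with fixed and dilated pupils. The 30% has no horizon either, and deaths are followed for three months. This stands.

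**The direction of bias is not shown.** It is tempting to say that the arm with more early deaths would lose its largest clots and appear to clear blood better. Nothing in the document establishes this. In the simulation the arm difference barely changed, although that setting was not built around strongly unequal deaths and so does not rule it out.

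**The consequences are limited.** Secondary outcomes are descriptive, with no formal hypothesis tests. This stands and limits the weight of the point.

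**A journal article leaves detail to the full protocol or analysis plan.** That would excuse silence. Here the article states a premise and a rule for every analysis, and the premise conflicts with its own planning figure.

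**Conclusion.** The point holds in a limited form. Expecting few, completely random missing values conflicts with a sample size that needs a 30% allowance for death, as far as CT volumes through day 8 are concerned. Complete-case analysis without exception is then the wrong rule for those data. Taken at patient level, it excludes randomised patients who have usable early scans, contrary to intention to treat.

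The size depends on mortality by day 8, which is not stated. On an assumed 10% to 30%, and on the patient-level reading, about 52 to 41 of 58 patients remain. The amount and direction of any between-arm bias cannot be derived.

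The primary time-to-occlusion analysis is not affected by this point. Nor does the point extend to the 90-day functional scales: a reader might infer that deaths are treated as missing there and call for imputation, but the document does not say so. The change is worth making for a descriptive secondary endpoint; it does not threaten the trial's main result.

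**What to change.** 1. Delete the statement that missing values occur completely at random.
2. Exempt the repeated CT volumes from the complete-case rule. State that the linear mixed model is fitted by likelihood (REML) to all available scans of all randomised patients, and that this is valid under missing at random.
3. Optionally, report the number of scans by arm and visit with the reason for each missing one (death, discharge, withdrawal), and add a simple sensitivity analysis for truncation by death. The second item is useful because the model in step 2 implicitly continues volume trajectories beyond death.

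Steps 1 and 2 are changes of wording and need no new data or patients. Step 3 adds one table and a modest amount of analysis.
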